### Randomization

Patients who meet the inclusion criteria and have provided informed consent will have their fractures classified according to the system proposed by Magerl et al. The randomization process will be performed for each fracture type (A, B and C). The patients will be randomly allocated into the following two groups: A- conventional open surgery and B- minimally invasive percutaneous surgery. The randomization will be performed via a centralized system. The research team will contact the central randomization system informing the type of fracture (A, B or C). The type of treatment will then be assigned by this system, with the patient being subsequently allocated to the appropriate group. We will use envelopes for each fracture type, following the CONSORT (Consolidated Standards of Reporting Trials) guidelines. The randomization will be performed using numbers generated by a specific software [MedCalc Statistical Software version 18.11.3] and will obey the 1:1 ratio for each group [MedCalc Software bvba, Ostend, Belgium; https://www.medcalc.org; 2019].”general anesthesia. Stability of the spine will be achieved by bilateral short-segment pedicle instrumentation. Pedicle screws will be inserted into the vertebral body one level above and below the fractured vertebra. The fractured vertebra will also be included in the fixation. In the fractured vertebra, a short pedicle screw will be inserted uni- or bilaterally according to the degree of pedicle involvement.

The spine fixation system is composed of a 6.5-mm-diameter polyaxial pedicle screw attached to 5.5 mm rods. The vertebral fixation system will be applied through the conventional open approach in group A (open approach) and percutaneously without open exposition of the injured vertebral segment in group B (minimally invasive percutaneous surgery). Posterior fusion using bone grafts or bone substitutes will not be performed in either group. External immobilization will not be used after surgery, and the patients will be allowed to walk according to their general clinical picture and pain.

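### The Randomization section does not say how its envelopes relate to the central system, and the preoperative VAS is placed after allocation in one section but around consent in two others

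*Protocol article*

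**What the plan says.** Protocol article, Randomization: "The randomization will be performed via a centralized system". The team reports the fracture type to that system, and "The type of treatment will then be assigned by this system, with the patient being subsequently allocated to the appropriate group". The next sentence begins "We will use envelopes for each fracture type" and refers to CONSORT. The section then says "The randomization will be performed using numbers generated by a specific software" and that the allocation "will obey the 1:1 ratio for each group". Consent, eligibility and classification of the fracture come before allocation.

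On baseline scores, the article speaks in three places:

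- Patient selection mentions signing of consent and then collection of preoperative baseline data, including the outcome scores.
- Informed consent and patient safety repeats that pairing.
- Outcome measurements says that demographic, clinical and radiographic data are taken at admission. The preoperative parameters of Table 2 are to be acquired after randomization, allocation to a group and definition of the treatment. Table 2 includes pain (VAS), SF-36, EuroQol and HADS.

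**The concern.** Two ways of delivering the allocation stand in adjacent sentences, and the reader is not told whether they are one procedure or two. The difference matters because they protect the sequence by different means. A central system can withhold the assignment until the patient is registered. An envelope does so only while its custody is controlled. If someone can learn the next assignment before enrolment is final, that knowledge can influence who is enrolled, or how a borderline fracture is classified, and the groups are then no longer comparable by design.

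The timing of the baseline belongs with this point because the moment of release decides whether a score counts as a baseline. If a patient marks the preoperative VAS after learning which operation is planned, that mark may be affected by the assignment. Any outcome defined as a reduction from it then carries the effect.

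**Working it through.** There is no figure on allocation to recompute, so the check sets the statements side by side.

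**1. Which arrangements fit the Randomization section?**

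| Arrangement | Central assignment sentence | Envelope sentence |
|---|---|---|
| Central office draws from its own envelope series, one per fracture type | fits | fits |
| Central computer list, with central envelopes as backup | fits | fits, if backup is meant |
| Envelopes kept elsewhere and opened after contact with the centre | fits only if the contact merely registers the patient or names an envelope | fits |

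The first arrangement satisfies every sentence without strain. The third is not excluded, because no sentence says where the envelopes are held or what they are for. The reference to CONSORT does not say which arrangement is used.

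**2. When is the baseline VAS taken?** Patient selection, and Informed consent and patient safety, put baseline scores next to consent without fixing their order relative to randomization. Ethical considerations puts consent before randomization. Outcome measurements is the only section that states an order for the preoperative variables, and it puts them after allocation. That order cannot hold for all of Table 2. The table also lists Magerl fracture type, which the Randomization section needs before it can allocate.

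**3. What could a late baseline do?** The first sample size statement in Statistical considerations uses a two-point VAS reduction, expected in 50% of group B and 25% of group A. Assume that the reduction is measured from the preoperative score.

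- Let B be the baseline, P the postoperative score, and R = B − P. A patient counts if R ≥ 2.
- Suppose knowledge of the assignment shifts reported baselines in one group by d points relative to the other. In that group the recorded reduction is R + d, so the rule becomes R ≥ 2 − d.
- The between-group difference in mean reduction moves by exactly d. The second sample size statement targets a difference of one point. If that comparison is of change scores, the bias is d against a target of 1. If it is of postoperative scores alone, d does not enter.

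The documents give no information on d, neither its sign nor its size.

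**4. What does not change?** The stated 58 per group reproduces with the pooled two-proportion formula (mean proportion 0.375):

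[1.96 × √(2 × 0.375 × 0.625) + 0.84 × √(0.5 × 0.5 + 0.25 × 0.75)]² / 0.25² = (1.342 + 0.556)² / 0.0625 ≈ 57.6, rounded up to 58.

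The unpooled formula as printed gives 7.84 × 0.4375 / 0.0625 = 54.88, so 55; that gap is a separate matter. Neither calculation uses the allocation mechanism, so the choice of mechanism leaves sample size, alpha and power as they are.

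**The case against.** The Randomization section can be read as one coherent procedure: the caller gives the fracture type and the central office opens the next envelope for that type. Who holds the envelopes, and how they are sealed and numbered, is the kind of detail that a journal article leaves to the full protocol. The Outcome measurements sentence may also be loose wording, since the same section has fracture data collected at admission.

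Much of this stands. Missing envelope detail alone would be no finding, and the compatible reading is a natural one. What remains is that the article states two things about who or what delivers the allocation and does not join them, and that its only explicit order for the preoperative VAS is the undesirable one.

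A reader might infer more than the text supports:

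- That envelopes sit at the five centres, so that centre is an undeclared stratum. No sentence places them there, and the emphasis on a central system points the other way.
- That upcoming assignments can be guessed. The article mentions no blocks, and predictability would in any case come from small blocks within a site, not from envelopes as such.
- That the person who enrols the patient is the operating surgeon. The article speaks only of the research team.
- That concealment matters because the primary outcome is self-reported. Concealment guards against selection at enrolment whatever the outcome. Self-report bears on the baseline timing and on blinding.

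**Conclusion.** The point holds as a minor one. The description of allocation is unreconciled; it is not evidence that concealment fails. The baseline order is likewise unreconciled: one section puts the VAS after allocation, and two place baseline scores around consent without stating an order relative to randomization.

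The possible harm from a late baseline rests on three assumptions: that the score really is taken after allocation, that the patient then knows the assignment, and that the analysed outcome is a reduction from that score. The article states the first, does not address the second, and suggests the third in its sample size statement. No numerical consequence can be derived.

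**What to change.** State one mechanism in the Randomization section. The central system holds the sequence for each fracture type and releases an allocation only after consent, eligibility, fracture type and baseline VAS have been logged. Either delete the envelope sentence or say that the envelopes are held only at the central office.

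Align Outcome measurements so that the baseline patient-reported scores (VAS, SF-36, EuroQol, HADS) precede randomization, in keeping with the two consent-related sections. Since the article gives a study start of June 2017, add a sentence saying which mechanism and which order have been used for patients already randomized.

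The cost is a few sentences. The central system and all the scores are already planned. If the scores are in practice taken after allocation, they move earlier in the preoperative visit, and nothing is added to what is measured.

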### Outcome measurements

At admission, demographic, clinical and radiographic data for the patients will be obtained for characterization and classification of the fracture. After randomization, allocation of the patient into the study group and definition of the type of treatment to be performed, parameters related to the preoperative period will be acquired (Table 2).

**Table 2 Tab2:** Variables collected in the preoperative period

Level of fracture	
Neurological status (ASIA scale)	
Type of fracture (Magerl’s classification)	
Comorbidities	
Associated lesions	
Fracture of upper limbs	
Fracture of pelvis or lower limbs	
Charlson comorbidity index	
EUROQL-5	
Short-form SF-36	
HADS (Hospital Anxiety Depression Scale)	
Pain (VAS)	
AP Rx- vertebral alignment	
Lateral Rx- height of the fractured vertebral body, height of the vertebral body above and below the fractured vertebra, kyphosis of the injured vertebral segment, kyphosis of the fractured vertebra, sagittal index (Farcy index)	
CT- compression of the spinal canal, sagittal and coronal diameters of the spinal canal, lamina fracture	

Intra-operative parameters related to the surgical procedure will also be acquired (Table 3).

**Table 3 Tab3:** Variables collected in the intra-operative period, related to the surgical procedure

Type of approach (open/percutaneous)	
Operating time	
Intraoperative blood loss	
C-arm exposure	
Surgical drain	
Implants – mono or polyaxial screw/diameter/length/rods	
Intra-operative adverse events – (anesthesia, hemorrhage, dural lesion, neurological lesion)	
Intra-operative change of implants	

During the immediate postoperative period up to the moment of hospital discharge, data regarding the clinical evolution of the immediate postoperative period, use of analgesic medication, immediate postoperative complications, and postoperative imaging tests will be collected to evaluate the radiographic parameters (Table 4).

**Table 4 Tab4:** Variables collected in post-operative and hospital discharge parameter

Drainage – (48 h)	
VAS – 3 days postoperative	
Deambulation	
Complications – superficial infection, deep infection, neurological lesion, vascular lesion, hematoma	
Analgesics- drug, dosage, period of administration	
Antibiotics- drug, dosage, period of administration	
Number of the days from surgery till hospital discharge	
Adverse effects	
Reoperation	
AP Rx- vertebral alignment	
Lateral Rx- height of the fractured vertebral body, height of the vertebral body above and below the fractured vertebra, kyphosis of the injured vertebral segment, kyphosis of the fractured vertebra, sagittal index (Farcy index	
CT- compression of the spinal canal, sagittal and coronal diameters of the spinal canal, position of the screws inside the pedicle	

After hospital discharge, the patients will have follow-up visits at 1, 2, 3, 6, 12 and 24 months after surgery for clinical and radiological evaluations (Table 5).

**Table 5 Tab5:** Variables collected and to be evaluated during follow-up (1, 2, 3, 6, 12 and 24 months)

Short-form SF-36	
HADS	
Dennis’s pain scale	
Dennis’s work scale	
EUROQOL-5	
VAS	
Roland Morris Disability Questionnaire	
Complications	
Analgesics- drug, dosage, period of administration	
Adverse effects	
AP Rx- vertebral alignment, implant breakage, loosening	
Lateral Rx- height of the fractured vertebral body, height of the vertebral body above and below the fractured vertebra, kyphosis of the injured vertebral segment, kyphosis of the fractured vertebra, sagittal index (Farcy index), implant breakage, loosening	

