### Informed consent and patient safety

The patient will be asked to sign the informed consent form. Pre-operative baseline data will be collected for the outcome scores, patient demographic characteristics and classification and characterization of the injured vertebral segment. A patient who meets the inclusion criteria will be informed about the study. The therapeutic options as well as their benefits and risks will be explained, and the patient will be free to participate in the study. If the patient is willing to participate in the study, written informed consent will be obtained.

The patients will be notified that they are free to withdraw from the study at any time. Adverse effects or complications will be treated and followed up until the issue is stable or resolved. The study was submitted to and approved by an institutional review board (IRB) trial registration, ClinicalTrials.gov Protocol Registration and Results System (PRS): NCT03316703, Approval Number: 1.933.631, study start in june 1, 2017.

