### Primary outcome measure

The pain intensity after the surgical procedure will be evaluated using the VAS. The pain is related by the patient on a 100 mm horizontal visual analog scale. The two ends of the scale are 0 mm (no pain) and 100 mm (the most terrible pain that I can imagine). The patient will be asked to mark the scale based on their average pain during the evaluation period. The pain intensity will be evaluated before and after the surgical procedure. After surgery, pain will be evaluated on the first three postoperative days and at 1, 2, 3, 6, 12 and 24 months after the surgical procedure. Pain will also be evaluated according to Dennis’s scale at the 1, 2, 3, 6, 12 and 24 month follow-up visits.

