### Statistical considerations

#### Sample size

Considering an expected reduction of two points in the visual analog pain scale (VAS) in 50% of the patients in group B compared to 25% those in group A after surgery with a significance level of 5% and a study power of 80%, and using the Z statistic, where p_1_ (0.5) and p_2_ (0.25) are previously defined, a minimum sample size of 58 patients was obtained, for each of the groups, according to the following formula:
$$ \mathrm{n}={\left( Z\alpha / 2+{Z}_{\beta}\right)}^2\ast \left({p}_1\left( 1-{p}_1\right)+{p}_2\left( 1-{p}_2\right)\right)/{\left({p}_1-{p}_2\right)}^2 $$

Where, Zα/2 is the critical value of the Normal distribution at α/2, i.e., 0.05 and critical value =1.96; Z_β_ is the critical value of the Normal distribution at β, i.e., 0.2 and critical value = 0.84; p_1_ and p_2_ are the previously defined sample proportions of the two groups.

Assuming an alpha of 0.5, a sample size of 58 patients per group was calculated to yield a power of 80% and detect a difference of one point between intervention groups in the 10-point VAS score. Standard differences were estimated to be 1.6 according to previous work (1) and drop-out rates were anticipated to be 28%”.

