### Ethical considerations

The study was approved by the Institutional Review Committees (IRCs) of all participating centers that agreed with the proposed study protocol (Trial registration: NCT03316703). Informed consent will be obtained before randomization, and the patients are free to refuse participation. The patients will not receive financial rewards for taking part in the study, and they are free to withdraw from the study at any time without interruption of their treatment and medical care.

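### The only sentence that orders the pre-operative pain and quality-of-life scores relative to randomisation puts them after allocation, and it needs reconciling with the consent and randomisation sections

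*Protocol article*

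**What the plan says.** The Outcome measurements section describes two steps. The first is "At admission, demographic, clinical and radiographic data for the patients will be obtained for characterization and classification of the fracture"; no patient-reported score is named there. The second opens with "After randomization, allocation of the patient into the study group and definition of the type of treatment to be performed, parameters related"; the rest of that sentence says that the Table 2 set is acquired at this point. That table lists VAS pain, SF-36, EuroQol and HADS together with comorbidity, neurological status, imaging measurements and the Magerl fracture type.

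The sections on Patient selection and on Informed consent and patient safety both carry a sentence on baseline data: "Pre-operative baseline data will be collected for the outcome scores, patient demographic characteristics and classification and characterization of the injured vertebral segment". It stands beside the consent text, but says only that the data are pre-operative. Ethical considerations adds "Informed consent will be obtained before randomization", and Randomization says "The research team will contact the central randomization system informing the type of fracture (A, B or C").

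On use of the scores, the Primary outcome measure section states "The pain intensity will be evaluated before and after the surgical procedure". The Sample size section begins "Considering an expected reduction of two points in the visual analog pain scale (VAS) in 50% of the patients in group B", against 25% in group A.

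**The concern.** Baseline pain and quality of life are self-reported, and patients are told beforehand about the possible advantages and disadvantages of the treatment. The Background and Discussion sections describe the percutaneous approach as causing less pain. If a patient marks the baseline VAS after the approach has been assigned, the mark can be influenced by knowing it. The document describes nothing that conceals the allocation from the patient or from the person collecting the scores.

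A baseline taken after allocation is no longer protected by randomisation. If one arm reports it higher or lower because of the assignment, the distortion passes into anything computed from it:

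- a reduction from the pre-operative VAS, or a responder status based on that reduction;
- the relative-risk analysis in the Primary outcome analysis section, if the event is that reduction;
- the within-group paired t tests in the Statistical analysis section.

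**Working it through.** **1. Order of measurement**

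| Section | Baseline scores | Order relative to randomisation |
|---|---|---|
| Patient selection; Informed consent and patient safety | Mentioned beside consent | Not stated; pre-operative only |
| Ethical considerations | Not mentioned | Consent comes first |
| Randomization | Not mentioned | Fracture type is needed before allocation |
| Outcome measurements, with Table 2 | VAS, SF-36, EuroQol, HADS | After randomisation, allocation and definition of treatment |

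Only the last row gives an explicit order for the scores. It also covers fracture type, because Table 2 lists it, and for that item the order is impossible. The sections do not fit together as written.

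**2. The plan's own figure**

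Inputs from Sample size: p1 = 0.50, p2 = 0.25, z = 1.96 and 0.84. The stated result is 58 per group.

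- Pooled-variance formula, with mean proportion 0.375: [1.96 × √(2 × 0.375 × 0.625) + 0.84 × √(0.25 + 0.1875)]² / 0.25² = (1.342 + 0.556)² / 0.0625 ≈ 57.6, so 58. This reproduces the figure; power at 58 per group is 80.2%.
- The formula as printed (unpooled): 2.8² × 0.4375 / 0.0625 = 54.88, so 55. That is a separate matter.

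The order of measurement does not enter either formula, so correcting it leaves 58 unchanged.

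**3. Illustration of sensitivity**

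Assumptions not given by the documents:

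- the reduction in VAS is normally distributed;
- there is no true difference, and 25% of each arm are responders;
- one arm over-reports its baseline by b points;
- the SD of the change is s. The value 1.6 is borrowed from the second calculation in Sample size, which does not call it an SD of change; 2.5 is assumed outright.

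Responder rate in the shifted arm = Φ(Φ⁻¹(0.25) + b/s), with Φ⁻¹(0.25) = −0.6745.

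| b | s | Argument | Responder rate |
|---|---|---|---|
| 0.3 | 2.5 | −0.6745 + 0.12 = −0.5545 | 29.0% |
| 0.5 | 2.5 | −0.6745 + 0.20 = −0.4745 | 31.8% |
| 0.5 | 1.6 | −0.6745 + 0.3125 = −0.3620 | 35.9% |

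The spurious difference runs from 29.0 − 25 = 4 to 35.9 − 25 = 11 percentage points, against a design difference of 25. With b = 0.5 and 58 per group, a two-sided 5% test of two proportions would reject with probability about 13% (s = 2.5) to 25% (s = 1.6).

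**The case against.** The strongest reply is that the Table 2 sentence is loose narrative in a condensed article. It cannot be literally true of fracture type, and the consent sections put baseline scores where one would expect them, so sites may well collect them before allocation. This stands in part: the article does not establish what sites do, and a reader who infers that every baseline score is certainly taken after allocation goes beyond the text. But loose wording does not move the questionnaires earlier, and the consent sections never say that they come before randomisation.

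A second reply concerns the endpoint. A reader might infer that the bias enters the primary outcome directly. The Abstract, Methods/design and Primary outcome measure sections describe that outcome as postoperative VAS pain, and the Statistical analysis section provides an independent-samples t test between groups. The second sample-size statement, a one-point difference between groups, needs no baseline. The two-point reduction appears only in the first sample-size rationale, which does not name its reference value. The relative-risk analysis makes a responder endpoint plausible without defining one. Nor is baseline VAS among the adjustment variables named in the section on secondary endpoints. This reply stands: the bias is conditional on an analysis that uses the pre-operative score.

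Third, neither the existence nor the direction of any shift is shown, and silence on blinding in an article is weak evidence. That too stands, and it limits the claim to a possible influence.

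**Conclusion.** The point holds as an inconsistency with an avoidable risk of bias. The one explicit statement of order puts the self-reported baseline after allocation, it conflicts with the Randomization section for fracture type, and the consent sections do not settle the question. Analyses of change, of responder status or of paired differences would be exposed; a plain comparison of postoperative VAS would not.

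The size cannot be derived from the documents. The rise from 25% to about 29% to 36% rests on an assumed shift of 0.3 to 0.5 points in one arm and an assumed SD of change of 1.6 to 2.5. It shows that a modest shift would matter for a change-based endpoint, not that one occurs. A shift in the opposite direction would distort the comparison the other way. The sample size is unaffected.

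**What to change.** Reconcile Patient selection, Informed consent and patient safety, and Outcome measurements with one sentence: *The patient-reported baseline scores (VAS, SF-36, EuroQol, HADS) are completed after consent and before the randomisation system is contacted.* Have completion confirmed when the randomisation request is made. This fits the central system and envelopes already described and needs no link to the data-management platform. The Table 2 text should also say that fracture type is fixed before the request.

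The change can be confined to the self-reported scores; the concern does not require the detailed imaging measurements to be moved. The cost is a small reordering of existing steps, with no extra visit or assessment and no change in sample size.
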